### Secondary endpoints

The secondary endpoints are technical success, complications, operation time, pain during treatment, disease-specific quality of life, time to return to daily activities and/or work, and cost-efficiency analyses after RFA or MOCA.

### Ethical considerations

A patient who meets the entry criteria is fully informed about the trial and provided with a patient information and consent form. Patients willing to participate in the study are included after signing the informed consent form. This study is conducted in accordance with the principles of the Declaration of Helsinki and Good Clinical Practice guidelines. The study is approved by the Medical Ethics committee of Nijmegen (CMO 2011/091) and the local institutional board of each participating center.

### Safety and quality control

#### Data safety monitoring board

The Data Safety Monitoring Board (DSMB) will review safety and make recommendations regarding the conduct of the study to the steering committee, and to the accredited Medical Ethical Board (METC) that approved the study protocol. An interim safety analysis will be performed at six-months after initiation of the trail. This analysis will include at least 75 patients.

#### Adverse and severe adverse events

Adverse events (AE) are defined as any undesirable experience occurring to a participant during the study, whether considered related to the investigational device or not. This definition includes events occurring during a hospital stay of up to 30 days of follow-up. Any underlying disease that was present at the time of enrollment is not reported as an AE, but any increase in the severity of the underlying disease will be reported as an AE. All AEs will be monitored from the time of enrolment through the 30-day follow-up visit. AEs will be recorded on the case record forms. A description of the event, including the start date, end date, action taken, and the outcome will be provided.

A severe adverse event is any event leading to death, deep venous thrombosis, and neurological complications.

Data on AEs will be reported to the DSMB and to the accredited METC via 'Toetsingonline’ on the website of the Central Committee on Research involving Human Subjects (CCMO).

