The safety and efficacy of MOCA was shown in the first human study [19]. In this study, 30 patients with primary GSV insufficiency were treated using sodium tetradecyl sulfate (Sotradecol). At six months the anatomical success was 97% [19]. After a follow-up period of two years, 27 of the 28 (anatomical success 96%) treated GSV were occluded [20]. Several reports have confirmed the efficacy of MOCA, with occlusion rates varying from 94 to 97% [21-23]. No major complications such as deep vein thrombosis, pulmonary embolism or nerve injury were observed in all previous studies. Moreover, MOCA was associated with lower post-procedural pain and faster recovery than RFA [24]. To date, no studies have been performed to compare MOCA with other endovenous techniques in the treatment of varicose veins. The current study has been designed to compare MOCA for the treatment of GSV insufficiency to RFA in a multicenter randomized controlled trial.

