### Definitions of terms used for the study

Anatomical success: occlusion of the treated GSV segment, measured with duplex.

Clinical success: objective improvement of clinical outcome after treatment, measured with the Venous Clinical Severity Score (VSCC) of at least 1.

Technical success: initial technical success rate of the procedure, where the catheter can be safely placed at a defined distance from the saphenofemoral junction and the GSV can be treated without technical problems.

Failure of treatment: type 1 (non-occlusion) - the treated vein failed to occlude initially and never occluded during the follow-up; type 2 (recanalization) - the treated vein occluded directly after treatment, but recanalized, partly (>10 cm) or completely, at a later time point during follow-up; type 2a - recanalization of the entire treated segment of the vein; type 2b - partial recanalization (open segment > 10 cm).

Post-procedural complications: complications occurring within 30 days after treatment. Major complications to include deep venous thrombosis, pulmonary embolism, skin burn, saphenous neuralgia. Minor complications to include ecchymosis, superficial phlebitis, hyperpigmentation, induration, wound infection of the puncture site, prolonged pain > one week. Sclerosans-related complications.

Operation time: time of the procedure, starting from puncture of the vein to extracting of the catheter, skin-to-skin contact.

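### The closed definition of a severe adverse event leaves out non-fatal pulmonary embolism and skin burn, which the same article lists as major complications

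*Protocol article*

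**What the plan says.** The protocol article classifies harm in two places.

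Under *Adverse and severe adverse events*, the general category is wide: "Adverse events (AE) are defined as any undesirable experience occurring to a participant during the study". The severe category is a short list without a general criterion: "A severe adverse event is any event leading to death, deep venous thrombosis, and neurological complications". The collection period is also stated there: "All AEs will be monitored from the time of enrolment through the 30-day follow-up visit". On reporting, it says: "Data on AEs will be reported to the DSMB and to the accredited METC".

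Under *Definitions of terms used for the study*, the window is "Post-procedural complications: complications occurring within 30 days after treatment", and the upper grade is given as follows: "Major complications to include deep venous thrombosis, pulmonary embolism, skin burn, saphenous neuralgia". A list of minor complications comes next, and sclerosant-related complications are named at the end without a grade.

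Three other places bear on the point. *Secondary endpoints* includes complications. *Data safety monitoring board* says that the board "will review safety and make recommendations regarding the conduct of the study to the steering committee", and provides for one interim safety analysis. *Background* describes earlier work on mechanochemical ablation (MOCA) thus: "No major complications such as deep vein thrombosis, pulmonary embolism or nerve injury were observed in all previous studies".

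**The concern.** The severe category reads as complete: an event that leads to none of the three named outcomes is not severe. Yet the article elsewhere treats pulmonary embolism as major on the same footing as deep venous thrombosis, and also lists skin burn as major. A deep venous thrombosis is therefore both severe and major, while a survived pulmonary embolism is major only. Nothing in the text explains that ordering.

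What is at stake is the coherence of the safety reporting. If severe adverse events and major complications are both tabulated, the two tables will class the same patients differently, and a reader who sees only the severe table will see too few. The omission is also not neutral between arms. Radiofrequency ablation (RFA) heats the vein and MOCA does not, so a severe category that excludes skin burn leaves out a harm expected almost entirely in the comparator.

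**Working it through.** No figure in the plan needs reproducing. The check sets the two definitions side by side and then traces where each event is recorded.

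**Step 1. How to read the severe definition.** Its three items are joined by *and*. Taken literally, an event would need all three outcomes, which cannot be meant. I read it as any one of death, deep venous thrombosis or a neurological complication.

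**Step 2. The listed major complications against that definition.**

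| Event | Major complication | Severe adverse event | Adverse event |
|---|---|---|---|
| Deep venous thrombosis | yes | yes, named | yes |
| Saphenous neuralgia | yes | yes, as a neurological complication | yes |
| Pulmonary embolism, survived | yes | no, unless another listed outcome results | yes |
| Skin burn | yes | no, unless a listed outcome results | yes |

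Two of the four match and two do not. The mismatch also runs the other way: death, and neurological complications other than saphenous neuralgia, are in the severe definition but not among the major complications. Neither category contains the other.

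**Step 3. Which arm is affected.** *Treatment details* describes heating of the vein wall for RFA, and *Background* states that MOCA does not heat it. The missing skin burn would therefore lower the severe tally mainly in the RFA arm. Polidocanol is given only in the MOCA arm, and sclerosant-related complications carry no grade. A serious sclerosant reaction thus meets the severe definition only if it leads to one of the three named outcomes. The directions follow from the treatments. The sizes are unknown, because the article gives no rate for any of these events.

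**Step 4. Where the events still appear.** Both unmatched events are adverse events under the wide definition, and each is recorded on the case record form with its dates, handling and outcome. Adverse event data go to the DSMB and the ethics committee. Both events also count in the complications endpoint, as do sclerosant-related complications. Only the severe label is lost.

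**Step 5. The window.** Adverse events are followed to a 30-day visit, and complications are counted to day 30. Table 1 has no 30-day visit; the nearest is at 4 weeks, which is 4 × 7 = 28 days. If that is the visit meant, the last 30 − 28 = 2 days of the complication window have no scheduled contact.

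**The case against.** The strongest reply is that the two labels serve different purposes and that the article never equates them. A count made under the severe definition would be correct by that definition, only narrower than the count of major complications. The *Background* sentence reports earlier studies and is not a grading rule for this trial. A condensed article may also leave the general seriousness criteria and visit windows to the full protocol, and *Ethical considerations* states conduct under Good Clinical Practice. Much of this stands. It does not remove the conflict, because the article states both definitions outright and gives no reason why they differ. This is more than missing detail.

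Three stronger readings are tempting, and the documents do not support them.

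- A reader might infer that the DSMB would be misled or would work from a wrong count. The board receives data on all adverse events, and no threshold, stopping boundary or decision is tied to a severe-event count.
- A reader might infer that the between-arm safety comparison is distorted. That comparison is served by the complications endpoint, which already includes pulmonary embolism, skin burn and sclerosant-related events. Only a tally of severe adverse events, which is not a named endpoint, would be affected.
- A reader might assume an event rate to size the problem. At an assumed 0.5%, for example, 230 patients give 230 × 0.005 = 1.15 expected events and a chance of 1 − 0.995^230 = 0.68 of at least one. This shows only that an event may occur. The rate has no source in the article, and the case would still be recorded, reported and counted as a complication.

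The two-day difference between the visit and the window is trivial, and no effect on a result can be shown.

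**Conclusion.** The point holds as an inconsistency in severity classification. Two of the four listed major complications fall outside the severe definition, so a severe adverse event table would under-classify them and disagree with a major complication table. The skin burn part would fall mainly on the RFA arm. The number of patients affected cannot be computed from the documents.

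The conclusion assumes that the severe definition is meant as a complete list with its items as alternatives, and that saphenous neuralgia counts as a neurological complication. If the second assumption failed, the mismatch would widen to three of four.

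The events are not hidden. No primary endpoint, sample size or stated DSMB decision is affected. The correction is worth making because it is cheap and because the present wording invites two conflicting safety tables.

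**What to change.** Reconcile the two sections with one definition. A severe adverse event would be one that meets any general seriousness criterion (death, threat to life, unplanned or prolonged hospital admission, persistent disability), *or* is any major complication in the definitions section, *or* is another neurological complication, so that nothing now covered is lost. The general criteria are needed as well as the list. Adding the list alone would bring in skin burn, which bears on the RFA arm, but would do nothing for a serious sclerosant reaction in the MOCA arm. If the two categories are meant to differ, say so and give the reason.

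As a minor edit, make the end of adverse event collection and the complication window agree with Table 1. Either add a contact at or after day 30, or tie both to the 4-week visit.

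The cost is wording in the safety section and a few more events classed as severe. If day 30 is kept, there is also one brief contact per patient. Recruitment had begun by the time of the article, but all adverse events are recorded with their details, so those already collected can be reclassified from the case record forms. Treatment, endpoints and sample size are unchanged.

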### Inclusion criteria

The inclusion criteria are: primary GSV incompetence; C2 to C5 varicose veins; diameter of the GSV at the saphenofemoral junction ≥ 3 or ≤ 12 millimeter; aged between 18 and 80 years; andwritten informed consent.

### Exclusion criteria

The exclusion criteria are: C6 varicose veins; previous surgery or treatment for varicose veins (such as a crossectomy, surgical strip, or thermal ablative procedure); oral anticoagulant; pregnancy or lactation; previous deep venous thrombosis; immobilization; contraindication or known allergy for sclerosant; coagulation disorders or an increased risk of thromboembolism; severe renal insufficiency; and/or severe liver insufficiency.

### Recruitment

A total of 460 patients with primary great saphenous incompetence are to be included in the MARADONA trial after signing informed consent (Figure 1). The pre-procedural status will be determined by the Clinical Etiology Anatomy Pathophysiology (CEAP) score [25] and VCSS [26].

**Figure 1 F1:**
[figure not shown]
**This figure illustrates the study design.** A total of 460 patients will be randomized to radiofrequency ablation (N = 230) or mechanochemical endovenous ablation (N = 230). GSV, great saphenous vein.

After randomization, the GSV is obliterated in day treatment: study arm 1: (RFA); study arm 2: (MOCA).

### Randomization

Randomization will be performed during the outpatient department visit in which the patient is included. Patients will be randomized by the responsible surgeon to one of the treatment arms, using a web-based randomization tool (Research Manager, NOVA Business Software, Zwolle, The Netherlands). Randomization will be performed by blocks with stratification for participating centers.

### Treatment details

#### Radiofrequency ablation (RFA)

During RFA, radiofrequent energy is used to heat the vein wall of the GSV. The catheter is inserted into the vein and direct energy is delivered to the endothelium with the result of collapsing and sealing the vein. During the MARADONA study, all participating centers are using the VNUS ClosureFAST™ catheter (VNUS Medical Technologies, San Jose, California, United States). The VNUS ClosureFAST™ catheter contains a 7 cm long heating element at the end of the catheter, used for 'segmental’ ablation. A temperature of 120°C is generated in the heating element during a 20 second treatment cycle.

The insufficient GSV is punctured, ultrasound-guided, and a guidewire inserted. An introducer sheath is placed over the guidewire. The catheter is then introduced and positioned 2 cm distal to the saphenofemoral junction using ultrasound guidance. The tumescence anesthesia is delivered along the entire segment to be treated. An approximate volume of 10 mL per centimeter-treated vein is used. The patient is placed in a horizontal position and the catheter is activated. Every 20 seconds a new 7 cm segment of the GSV is treated after withdrawal. The most proximal segment of the GSV is treated with two cycles as recommended by the manufacturer. This process is repeated until the entire incompetent vein is ablated. After treatment, the deep venous system is controlled by ultrasound.

A compression stocking (20 to 30 mmHg) will be applied continuously for 24 hours and then daily for two weeks. Patients may resume normal activities immediately after the procedure. No concomitant phlebectomies or additional sclerotherapy is performed.

#### Mechanochemical endovenous ablation (MOCA)

During MOCA, the ClariVein® device is used to induce a combination of mechanical and chemical damage to the vein wall. The ClariVein® device is an infusion catheter which is designed to administer a sclerosant in the incompetent vein through an opening at the end of the catheter. An iron wire extends through the whole catheter, with a small iron ball at the end. The purpose of the rotating wirer is fourfold: (1) promoting the coagulation activation by minimal mechanical damage to the endothelium, (2) inducing a vasospasm which reduces the diameter of the vein, (3) increasing the action of sclerosant by an increase in surface, (4) ensuring an even distribution of the sclerosant at the endothelium. The catheter together with the iron wire is connected to a motorized handle that allows for the rotation of the metal wire.

The insufficient GSV is punctured, ultrasound-guided and a guidewire inserted. A 4 Fr introduction sheath is introduced and subsequently the ClariVein® catheter is inserted and the tip of the iron wire is placed near the saphenofemoral junction, 0.5 cm below the superficial epigastric vein, as verified by ultrasound. The patient is treated in a horizontal position. The wire is then activated for 10 seconds in order to induce vasospasm. The device is slowly withdrawn with a speed of about 7 seconds per centimeter, while the sclerosant is continuously injected using 2 mL 3% polidocanol for the first 10 to 15 cm and 1.5% polidocanol for the remainder of the GSV. After treatment, the deep venous system is controlled with ultrasound. A compression stocking (20 to 30 mmHg) will be applied continuously for 24 hours and then daily for two weeks. Patients may resume normal activities immediately after the procedure. No concomitant phlebectomies or additional sclerotherapy is performed.

Polidocanol (Aethoxysklerol) is used as sclerosant, which is the only registered sclerosant in the Netherlands and is regularly used for sclerotherapy of reticular veins. The maximum amount of polidocanol depends on the weight of the patient, and will always be less than 2 mg/kg. Prior to treatment, the maximum allowable amount of polidocanol is determined for each patient. Then the length of the treated vein is measured. Both values are listed on the case report forms.

### Follow-up treatment periods

After four weeks, one, two and five years, patients are seen at the outpatient clinic to observe anatomical and clinical success (Table 1). Ultrasound duplex imaging, VCSS, CEAP score and quality of life scores are measured at all above mentioned time points. Ultrasound duplex imaging is done according to a standardized protocol for all participating hospitals.

**Table 1 T1:** Flow chart of the trial

	**Study period**					
	**Screening**	**Procedure**	**4 weeks**	**1 year**	**2 years**	**5 years**
**Outpatient visit**	X		X	X	X	X
**Physical examination**	X		X	X	X	X
**Informed consent**	X					
**Inclusion criteria**	X					
**Randomization**		X				
**CEAP/VCSS**	X		X	X	X	X
**Ultrasound**	X		X	X	X	X
**Pain score**		X				
**AVVQ**	X		X	X	X	X
**SF-36**	X		X	X	X	X

AVVQ: Aberdeen Varicose Vein Questionnaire; CEAP: Clinical Etiology Anatomy Pathophysiology classification; SF-36: Short Form 36-Item Health Survey; VCSS: Venous Clinical Severity Score.

Post-procedural pain is evaluated using a linear VAS score of 0–100 mm during 2 weeks after treatment. After the 4-week control any small branch varicosities may be treated when indicated.

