## Background

Varicose veins are a common problem in the Western world. Epidemiological studies show that 21% of adults have some form of varicose veins [1-3], with women being more affected than men [3,4]. The incidence of varicose veins increases steadily with age and is among the top ten complaints for which people visit their general practitioner. The main risk factors include: prolonged standing or sitting, pregnancy, sex and age [5]. The symptoms of varicose veins range from cosmetic complaints to venous ulcers [6].

High ligation and stripping of the great saphenous vein (GSV) has been the gold standard for GSV incompetence for more than 100 years [7]. Surgery is performed under general or spinal anesthesia and is related to a high recurrence rate of 18 to 40% after five years [8,9]. In addition, surgery may lead to significant postoperative symptoms (particularly pain and hematoma) and carries a risk of injury to the saphenous nerve [10,11].

Endovenous techniques have been developed for the treatment of varicose veins [12]. Endovenous laser ablation (EVLA) and radiofrequency ablation (RFA) are now widely accepted techniques and are frequently used in practice [13,14]. They are related to less hematoma, pain, and superior cosmetics and earlier resumption of normal activities and work when compared to traditional surgical stripping [15,16]. Thermal ablative modalities, however, carry the risk of damaging the surrounding tissues of the vein. For this reason, patients are treated with tumescence anesthesia, which requires multiple punctures around the vein. Despite the use of tumescence anesthesia there are still a subset of patients who have postoperative pain, which can last for weeks [17,18].

Mechanochemical endovenous ablation (MOCA), using the ClariVein® device (Vascular Insights, Madison, CT, United States), uses a rotating wire in a catheter to create mechanical damage to the endothelium of the vessel. At the same time, a sclerosant is infused at the end of the catheter, causing chemical damage to the vein wall. With MOCA, the vein wall is not heated and tumescence anesthesia is redundant. Subsequently complications that occur in thermal ablative modalities such as pain, hematoma, induration and nerve injury could be reduced.

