### Sample size calculation

The assumption has been made that MOCA will have a similar anatomical and clinical success rate at one year when compared to RFA. For a non-inferiority trial with an effect size (anatomical success) of 93% and a margin of 7%, 210 patients per group are needed (alpha 5%, power 80%). The effect size of 93% refers to an estimated anatomical success rate at a one year follow-up period for both groups. Taking into account 10% dropouts in each arm, 230 patients need to be included in each study arm.

A sample size calculation will also be performed for the second primary endpoint on the hypothesis that MOCA will have lower post-procedural pain, as measured by a 100-point VAS (Visual Analog Scale) score during the first two weeks after surgery. To evaluate a 30% reduction in post-procedural pain, 58 patients per group are needed (alpha 5%, power 80%). This analysis will be performed after the inclusion and randomization of at least all 58 patients in each group.

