### Primary endpoints

The primary endpoints are anatomic and clinical success and post-procedural pain after treatment for GSV incompetence with RFA or MOCA. Anatomic success will be measured one year after treatment using duplex ultrasonography. Clinical success will be measured using the Venous Clinical Severity Score (VCSS). Post-procedural pain will be evaluated using a 100-point VAS during the first two weeks after the treatment.

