### Quality of life scores

The Short Form-36 (SF-36) is a multidimensional measurement of general health. It yields eight domains of functional health and well-being scores. The 'Dutch translated’ Aberdeen Varicose Vein Questionnaire [27] (AVVQ) is a validated disease-specific quality of life measurement for chronic venous insufficiency.

Both questionnaires are completed preoperatively, after 4 weeks, one, two, and five years of follow-up.

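### Pain is a primary endpoint, but no VAS is scheduled before treatment or at the 4-week visit; two form lines would add modest precision and put later pain on the primary scale

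*Protocol article*

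**What the plan says.** Post-procedural pain is one of the primary endpoints. Under Primary endpoints the Protocol article says: "Post-procedural pain will be evaluated using a 100-point VAS during the first two weeks after the treatment". The note under Table 1 repeats the window: "Post-procedural pain is evaluated using a linear VAS score of 0–100 mm during 2 weeks after treatment". The sample size section uses the same two weeks. It asks for 58 patients per group to detect a 30% reduction at alpha 5% and 80% power, with the pain analysis to follow once at least that many have been randomised to each arm.

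In Table 1 the pain row has a single mark, under Procedure. CEAP/VCSS, AVVQ and SF-36 are marked at both screening and 4 weeks. The Quality of life section confirms this for the two questionnaires: "Both questionnaires are completed preoperatively, after 4 weeks, one, two, and five years of follow-up".

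Three other places bear on the point:

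- **Background**, on thermal ablation despite tumescence anaesthesia: "there are still a subset of patients who have postoperative pain, which can last for weeks".
- **Treatment details**, in the same words for RFA and MOCA: "A compression stocking (20 to 30 mmHg) will be applied continuously for 24 hours and then daily for two weeks".
- **Definitions**: "prolonged pain > one week" is listed as a minor complication, within a category defined as "complications occurring within 30 days after treatment".

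**The concern.** The instrument behind a primary endpoint is the only patient-status score in Table 1 with no pre-treatment value, although the visit at which it could be taken already exists. Patients enter with C2 to C5 disease, and the Background describes symptoms from cosmetic complaints upwards. They may therefore bring differing leg pain into the first post-treatment VAS. That variation stays in the error term, and no later analysis plan can adjust for a VAS that was never collected.

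The second half concerns duration. The article says that pain after thermal ablation lasts for weeks in some patients, yet VAS scoring stops at two weeks and the existing 4-week visit takes no score. At stake are the precision of the pain comparison at its planned minimum size, and the ability to describe longer-lasting pain on the scale used for the primary endpoint.

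**Working it through.** **1. The plan's own figure.** The article gives 58 per group but no mean or SD, so the number cannot be reproduced forwards. Solved backwards for a two-sided 5% test with 80% power:

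- d = (1.960 + 0.842) × √(2/58) = 0.520.
- For a 30% reduction, this implies SD/mean = 0.30/0.520 = 0.577 in the control arm.
- If alpha is one-sided (the article does not say), d = 0.462 and SD/mean = 0.650.

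The steps below use the two-sided value.

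**2. Gain if every patient has a screening VAS.** Adjustment for a baseline score with correlation r multiplies the residual variance by (1 − r²), so 58 patients have the precision of 58/(1 − r²). The article gives no r; the range is an assumption.

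| r | 1 − r² | 58 per group is worth | Power at 58 | n needed instead of 58 |
|---|---|---|---|---|
| 0 | 1.00 | 58 | 80.0% | 58 |
| 0.1 | 0.99 | 58.6 | 80.4% | 58 |
| 0.2 | 0.96 | 60.4 | 81.6% | 56 |
| 0.3 | 0.91 | 63.7 | 83.6% | 53 |
| 0.5 | 0.75 | 77.3 | 89.9% | 44 |

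**3. Allowing for patients already enrolled.** Trial status reports 50 patients randomised by December 2013. The minimum pain analysis has 2 × 58 = 116 patients, so 50/116 = 43% would lack the score and at most 66/116 = 57% would have it. The variance reduction then shrinks to about 0.57 × r²:

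- r = 0.3: 58/(1 − 0.57 × 0.09) = 61.
- r = 0.5: 58/(1 − 0.57 × 0.25) = 68.

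Power is Φ(d × √(n/2) − 1.96):

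- n = 61: 0.520 × 5.52 − 1.96 = 0.91, about 82%.
- n = 68: 0.520 × 5.83 − 1.96 = 1.07, about 86%.

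**4. At the full trial size.** With 210 per group and the same d, unadjusted power is already 99.96%, so adjustment adds nothing that matters for power.

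**5. What records pain after two weeks.** Set side by side:

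- **VAS:** nothing after two weeks.
- **Complications (Definitions):** pain beyond one week, within 30 days; no severity score is stated.
- **Adverse events:** followed to the 30-day visit, with a description, start and end dates, action and outcome.
- **AVVQ and SF-36:** completed before treatment and at 4 weeks.

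Later pain is therefore recorded in several forms, but none of them is the primary pain scale.

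**The case against.** The strongest reply is that nothing here is wrong. The two-week window is stated the same way in three places. The stated aim is less post-procedural pain, not less persistent pain, and the Background sentence concerns only a subset of patients. A reader might infer that the window contradicts the rationale. It does not: it limits the scope of the endpoint.

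A reader might also infer that the missing baseline biases the comparison, or that compression distorts it. Neither is supported. Allocation is randomised and stratified by centre, so prior leg pain is balanced in expectation and an unadjusted comparison is valid. The compression text is identical for both arms, so its overlap with the scoring window favours neither.

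Nor would it be right to say that pain after two weeks goes unmeasured, or that the complication item is a bare yes/no entry. The article does not describe its format, and adverse events carry start and end dates.

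Further, the baseline CEAP/VCSS, AVVQ and SF-36 could serve as covariates, and that choice may properly sit in an analysis plan that is not shown. Table 1 is also a compact flow chart: the mark under Procedure might cover a score just before treatment, though the article does not say so.

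All of this stands. It reduces the point to a design improvement. It does not remove it, because a VAS not collected at screening or at 4 weeks cannot be recovered later, and the other instruments are not the endpoint's own scale.

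**Conclusion.** This is a cheap improvement and not an error. The schedule states no pre-treatment VAS and takes none at 4 weeks. The cost is some precision at the planned minimum of 58 per group, and later pain is left to complication and adverse-event records and to the questionnaires.

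The size of the gain rests on an assumed correlation of 0.3 to 0.5. On that assumption 58 per group would be worth 64 to 77 with complete baseline scores, or about 61 to 68 if the 50 patients already randomised lack them. Below 0.3 the gain is under 4 points of power. At 210 per group, and at the effect implied by the plan's 58, it is negligible. The 61 to 68 is itself favourable, since any patient enrolled between December 2013 and the change would also lack the score. The pain comparison as planned remains valid, and these figures give no ground for calling it unsound.

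**What to change.** - Add one 100-mm VAS at screening, completed before randomisation. The Randomization section places allocation at the outpatient inclusion visit while Table 1 marks it under Procedure, so the form should state that the score comes first.
- Add one 100-mm VAS at the 4-week visit and report it by arm as a secondary outcome. The two-week primary window stays as it is.
- Adjust the two-week pain comparison for the screening VAS, with a missing-value indicator for patients enrolled before the change.
- Update Table 1 to show pain at screening, at the procedure, in the two weeks after, and at 4 weeks.

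The cost is two lines on forms for visits that already take place. The downside is missing baseline values for early patients; 460 − 50 = 410 of the planned patients were still to be randomised in December 2013.
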